## Abstract

**Background:** The Coronavirus disease 2019 (COVID-19) is the largest global epidemic in recent time. Chinese medicine has been recognized by the World Health Organization as an effective treatment for COVID-19, but there is still a lack of high-quality randomized, double-blind trials using placebo as the control to support its application, which may hinder its further promotion locally and internationally.

**Objectives:** This study will evaluate the efficacy and safety of Yinqiao Powder-Maxing Ganshi Decoction with variation in relieving major symptoms of mild and moderate COVID-19 by telemedicine.

**Methods and design:** This clinical study is a randomized, double-blind, placebo-controlled trial that applies telemedicine to evaluate the efficacy and safety of Yinqiao Powder-Maxing Ganshi Decoction in the treatment of mild and moderate COVID-19. Eligible subjects will be randomly divided into either treatment or placebo groups for up to 14 days after stratification according to age (A:18–49, B:50–65) and the number of vaccinations (a: ≥3 doses, b: ≤2 doses). The treatment group will receive Yinqiao Powder-Maxing Ganshi Decoction granules along with certain variation based on their symptoms, and the placebo group will receive the same amount of placebo granules. Subjects will be prescribed different additions based on their symptoms and pathogenesis at the inclusion. The oral temperature, oximeter, result of rapid antigen test and symptom score will be recorded by subjects until they have stopped the medication. Subjects are required to have follow-up assessment by video-conference on days 7, 14 and 35. The time for the body temperature returning to normal will be used as the primary outcome.

**Discussion:** This trial will provide scientific evidence on the use of Yinqiao Powder-Maxing Ganshi Decoction for the treatment of COVID-19, and the results would help raise the awareness in Hong Kong and the international community on the use of Chinese herbal medicine for treating COVID-19.

**Clinical Trial Registration:**
clinicaltrials.gov, identifier NCT05787327.

## Introduction

Coronavirus Disease 2019 (COVID-19), caused by the severe acute respiratory syndrome coronavirus 2 (SARS-CoV-2), has spread rapidly and is the largest worldwide epidemic in recent time. As at 25 June 2023, there were more than 767 million confirmed cases of COVID-19 globally, including more than 6.9 million deaths (World Health Organization, 2023).

Currently, western medicine including corticosteroids, antiviral drugs, immunomodulating agents, convalescent plasma therapy, anticoagulants and anti-inflammatory drugs are commonly used in the treatment of COVID-19 (Cascella et al., 2023). In Hong Kong, COVID-19 oral drugs (Paxlovid or Molnupiravir) would generally be prescribed in a hospital or clinic if the patient has no relevant contraindications and fulfills the clinical guidelines (COVID-19 patients age 60 years or older, high-risk groups, and people under age 60 years with chronic diseases) when the patient is diagnosed with COVID-19 and the onset of symptoms is within 5 days of presentation (Hospital Authority, 2023). Chinese medicine (CM) has a long history of preventing and curing disease and has played an important role in prevention and treatment of many epidemics. World Health Organization (WHO) launched a meeting on the use of CM in the treatment of COVID-19 in March 2022 (World Health Organization, 2022). It recognized the contribution of CM and encouraged adding CM to the existing treatment regimen for COVID-19. At the same time, the meeting also advocated to promote more international trials to further evaluate the effectiveness and safety of CM for COVID-19.

Currently, various CM interventional measures are available for COVID-19 treatment, of which the most famous are the “3 medicines and 3 formulations (三藥三方)”. “3 medicines (三藥)” mean 3 proprietary Chinese medicines, including Jinhua Qinggan Granule, Lianhua Qingwen Granule/Capsule and Xuebijing Injection Fluid; “3 formulations (三方)” are 3 herbal prescriptions, including Qingfei Paidu Decoction, Huashi Baidu Formula and Xuanfei Baidu Formula. The efficacy, safety and possible mechanism of “3 medicines and 3 formulations” have been supported and elucidated by a number of studies either used alone or in combination with usual care (Wang et al., 2020b; Cheng and Li, 2020; Duan et al., 2020; Liao et al., 2020; Zhao et al., 2020; Sun et al., 2021). Among the “3 medicines”, the composition of Jinhua Qinggan Granule and Lianhua Qingwen Granule/Capsule is modified from Yinqiao Powder and Maxing Ganshi Decoction; the composition of “3 formulations” also includes Maxing Ganshi Decoction. Yinqiao Powder and Maxing Ganshi Decoction are two well-known classical Chinese medicine prescriptions, and their efficacy in the treatment of lung diseases have been proven by many studies (Mei et al., 2014; Wang et al., 2020a; Li, 2020). Yinqiao Powder (from *Systematized Identification of Warm Diseases* 溫病條辨) is composed of ten botanical drugs, i.e., *Lonicerae Japonicae Flos* (Jin-yin-hua 金銀花), *Forsythiae Fructus* (Lian-qiao 連翹), *Platycodi Radix* (Jie-geng 桔梗), *Menthae Haplocalycis Herba* (Bo-he 薄荷), *Lophatheri Herba* (Dan-zhu-ye 淡竹葉), *Schizonepetae Spica* (Jing-jie-sui 荊芥穗), *Sojae Semen Praeparatum* (Dan-dou-chi 淡豆豉), *Arctii Fructus* (Niu-bang-zi 牛蒡子), *Phragmitis Rhizoma* (Lu-gen 蘆根) and *Glycyrrhizae Radix et Rhizoma* (Gan-cao 甘草), which can release the exterior with pungent-cool (辛涼透表) and clear heat-toxin (清熱解毒) (Wang, 2013). On the other hand, Maxing Ganshi Decoction (from *Treatise on Cold Damage and Miscellaneous Diseases* 傷寒雜病論) is a combination of three botanical drugs and one mineral drug, including *Ephedrae Herba* (Ma-huang 麻黃), *Armeniacae Semen Amarum* (Ku-xing-ren 苦杏仁), *Gypsum Fibrosum* (Shi-gao 石膏) and *Glycyrrhizae Radix et Rhizoma* (Gan-cao 甘草) which can diffuse the lung and discharge heat (宣肺泄熱) and suppress cough and calm panting (止咳平喘) (Zhang, 2013). A prospective randomized controlled trial showed that the combination of Yinqiao Powder and Maxing Ganshi Decoction were effective in reducing the time of fever resolution caused by influenza A virus H1N1 (Wang et al., 2011).

There has been much focus on CM for the treatment of influenza viruses and several correlational studies have been conducted on this topic. According to the experimental data, CM has the ability to inhibit virus replication by destroying the virus directly, interfering with virus adsorption and protecting cells from virus infection (Lu et al., 2008). In 2003, there was an outbreak of the Severe Acute Respiratory Syndrome (SARS). At that time, 40%–60% patients in the mainland received CM treatment alongside standard medical care, and good results were obtained (Leung, 2007). A research showed that CM could enhance immunoregulatory function and prevent infection effectively including SARS (Poon et al., 2006). According to CM theory, COVID-19 belongs to “pestilence (疫病)” (Zhang et al., 2020; Zhang, 2022; Zhi et al., 2022). The main clinical manifestation is fever, dry cough, fatigue and upper respiratory infection symptoms, which can be treated by the combination of Yinqiao Powder and Maxing Ganshi Decoction (National Health Commission of the People’s Republic of China, 2022). In fact, since the outbreak of the fifth wave of COVID-19 in Hong Kong, these two formulae have often been used with modifications by CM practitioners in the treatment of acute phase of COVID-19. The “Special Chinese Medicine Programme for COVID-19 In-patients” launched by the Hong Kong Hospital Authority clearly specifies the use of modified “Yinqiao Powder” and “Qingfei Paidu Decoction”, which include Maxing Ganshi Decoction, for the treatment of patients with specified types of CM patterns (證型) (Hospital Authority, 2022). However, there is still a lack of high-quality clinical evidence on the effectiveness and safety of the combination of Yinqiao Powder and Maxing Ganshi Decoction in the treatment of COVID-19. Therefore, this study will use the combination of these two formulae as the intervention for the treatment of COVID-19.

During the COVID-19 pandemic, telemedicine is one of the most effective ways of dealing with and controlling the COVID-19 in many countries, in order to ensure the continuity of care for patients with chronic diseases and timely supportive care for COVID-19 patients (Colbert et al., 2020). Patients are able to have the medical consultation by video-conference and receive the medication by delivery service, which can reduce the risk of transmission by minimizing direct contact. Therefore, telemedicine services have also been provided by the Hospital Authority (HA) and some private hospitals or clinics in Hong Kong (Whitehead, 2020). The fifth wave of the COVID-19 epidemic occurred in Hong Kong in 2022 has caused significant burden to the healthcare system. The Integrative Medical Centre of Hong Kong Institute of Integrative Medicine launched in the same year the “Free Telemedicine Consultation Service for COVID-19 Patients”, a programme providing CM treatment for COVID-19 patients through telemedicine. We plan to initiate a clinical study to test the effectiveness and safety of combined Yinqiao Powder and Maxing Ganshi Decoction for the treatment of COVID-19 patients.

## Study aim

The study aims to 1) evaluate the effectiveness and safety of Yinqiao Powder-Maxing Ganshi Decoction in the treatment of the major symptoms of mild and moderate COVID-19 patients by telemedicine; 2) provide a scientific rationale for the use of Yinqiao Powder-Maxing Ganshi Decoction in the treatment of COVID-19; 3) raise the awareness of Chinese medicine among COVID-19 patients and the wider community.

## Hypothesis

The combined Yinqiao Powder-Maxing Ganshi Decoction is superior to placebo in improving the major symptoms of mild and moderate COVID-19.

## Methodology

### Study design

This is a randomized, double-blinded, placebo-controlled trial via telemedicine. Eligible subjects will receive a maximum of 14 days’ treatment with Yinqiao Powder-Maxing Ganshi Decoction (with or without specified additions) or placebo, and will be followed up on days 7, 14 and 35 after receiving medication (day 0).

### Study population

Subjects who are diagnosed with COVID-19 by Rapid Antigen Tests (RATs) or PCR tests based on criteria of the Centre for Health Protection (CHP) of the Department of Health (DH), Hong Kong SAR, China will be recruited via telemedicine from the following clinics/Chinese medicine centres: 1) The CUHK Chinese Medicine Specialty Clinic and Teaching and Research Centre on CUHK campus (CUHK-CMSCTRC); 2) The two Integrative Medical Centres, Hong Kong Institute of Integrative Medicine at Shatin and Wan Chai respectively. Advertisements in the form of posters on the recruiting clinics/centres and internet platforms, such as Facebook, emails, instant messaging applications and websites will be made to facilitate community recruitment. Besides, we will publish articles in local newspapers and magazines as well as organize health promotion talks to augment the subject recruitment process. We will also seek to promote the trial in other suitable mass media if possible and necessary. Potential subjects who meet the eligibility criteria will be recruited.

### Eligibility

Subjects who fulfill all of the inclusion criteria and have none of the exclusion criteria will be recruited.

Potential suitable subjects with COVID-19 will be screened for the following eligibility criteria:

### Inclusion criteria

1. Age from 18 to 65 years;2. Tested positive for COVID-19 by RATs, Deep Throat Saliva (DTS) or Throat/Nasal swab RT-PCR tests;3. Patient diagnosed with mild to moderate COVID-19 based on the “Coronavirus disease 2019 (COVID-19) Treatment Guidelines” published by National Institutes of Health, United States;4. Duration of symptoms ≤72 h (Start from the presence of the major symptoms of COVID-19: Fever: oral temperature >37.2°C, or cough score ≥2, or fatigue score ≥2);5. At the moment of screening (or within 2 h before screening), body temperature: >37.2°C6. Diagnosed with pattern of wind and heat invading the exterior (風熱犯表證) and/or pattern of intense exuberance of lung heat (肺熱熾盛證) by a registered Chinese medicine practitioner (CMP) (Diagnostic criteria are the corresponding criteria in the “Diagnosis standards for common syndromes in traditional Chinese medicine (《中醫常見證診斷標準》)” published by “Diagnostic Subcommittee of China Association of Traditional Chinese Medicine (中華中醫藥學會中醫診斷學分會)” in 2008, with ≥20 as the threshold for determination);7. Explicit declaration of willingness to participate in the study at the time of video-conference screening after reading the electronic informed consent form (written consent form will have to be signed after inclusion).

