#### Baseline randomization (day −1 or 0)

Eligible subjects will be assessed by our registered CMPs via telemedicine in this trial, during which medical history and concomitant medication will be recorded. After stratification, subjects will be randomly assigned in a 1:1 ratio to receive up to 14 days of either modified Yinqiao Powder-Maxing Ganshi Decoction (about 33.4–59.7 g each day) or placebo granules (about 33.4–59.7 g each day). Specifically, the stratified randomisation is based on age (A: “18–49 years old” and B: “50–65 years old”) and the number of vaccination (a: “received 3 or more doses - fulfilling government vaccination requirement” and b: “received 2 doses or less of vaccine - yet to be fully vaccinated”). Subjects will be divided into two groups by age: one group is “18–49 years old” and the other one is “50–65 years old”; then they will be further divided into two groups within the different age group by the numbers of vaccination: one group is “received 3 or more doses of vaccine, and the another is “received 2 doses or less of vaccine”. Four subgroups will be created after stratification and subjects in each subgroup will be randomly assigned to either the treatment or placebo group. The distribution of age and number of vaccinations between the two groups will be roughly comparable after stratified randomisation. The IMP will be prescribed by Registered CMPs and will be sent to patients by delivery service. The current Western medicine treatment can continue during the study period.

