### Study outcomes

#### Assessment

1. The time between starting medication and body temperature returning to normal and the recurrence rate of fever after momentary recovery. Each subject will be issued with the same type of oral thermometer for measurement at 9 a.m. (±2 h) and 9 p.m. (±2 h) daily, with at least 12 h between each measurement. Normal oral temperature is defined as equal to or below 37.2°C. Temperature recovery time is defined as the total number of days between medication starting date and the date of “normal oral temperature for 24 h without antipyretic” (both days inclusive). Subjects are required to measure the temperature until day 14 or on the day when the temperature has remained normal for 24 h, whichever is later.2. The negative rate of RATs at day 14 and negative conversion time. Each subject will be issued with the same type of RAT kits which can be used for at least 14 days for testing at 9 a.m. (±2 h) each day, with at least 24 h between each test. Negative conversion time is defined as the total number of days between the medication starting date and the date of securing two successive negative RAT results (both days inclusive). Subjects were required to undergo testing until day 14 or the day when two successive negative RAT results at least 24 h apart are obtained, whichever is later.3. The remission rate at day 14 and remission time of major symptoms.4. The disappearance rates at day 14 and disappearance time of symptoms. Subjects are required to record the status of their symptoms including major clinical symptoms daily at 9 p.m. (±2 h). Except for fever which is marked as ‘No’ or ‘Yes’ according to whether the oral temperature exceeds 37.2°C, other symptoms will be graded on a scale of 0–4 from “None”, “Mild”, “Moderate”, “Severe” and “Very Severe” depending on the actual feelings of the subject (“None” means the symptom is not present, “Mild” means the symptom is present but does not interfere with daily activities; “Moderate” means the symptom is present and slightly interferes with daily activities; “Severe” means the symptom is present and most daily activities cannot be done; “Very Severe” means the symptom is present and interferes with all daily activities). Major clinical symptoms include fever, cough and fatigue. Remission is defined as oral temperature ≤37.2°C, cough and fatigue score ≤1; disappearance is defined as the symptom being present at day 0 (score >0) but the symptom score is 0 at the date of recording.5. All-cause mortality at the 21st day after stopping the medication.6. Incidence of the progression to severe or critical illness during the trial. The all-cause mortality at the 21st day after stopping the medication and the incidence of the progression to severe or critical illness during the trial will be confirmed by communication with the subjects and/or other related person(s) or checking their medical record in the Hospital Authority. The definitions of severe and critical illness are based on the related definitions of “Coronavirus disease 2019 (COVID-19) Treatment Guidelines” published by National Institutes of Health (severe illness: oxygen saturation in the indoor environment of sea level <94%, oxygenation index [PaO2/FiO2] < 300 mmHg, respiratory frequency >30 breaths/min, lung infiltrates >50%; critical illness: respiratory failure, septic shock, and/or multiorgan dysfunction or failure).7. Utilization rates of antipyretic, Paxlovid and molnupiravir within 14 days and the total dosage(s) of the drug(s) used. In this study, subjects are allowed to take western medicines prescribed for the treatment of COVID-19 under the current guidelines of the Hong Kong Hospital Authority with at least 2 h’ gap between Chinese and western medicines. If oral temperature >39.0°C and continues over 4 h; or the oral temperature >39.5°C, the patient is advised to take antipyretic (paracetamol is recommended as a priority) for acute treatment. Patients need to record the amount and time of the drug(s) used.8. Oxygen saturation. For safety reasons, each subject will be issued with the same type of pulse oximeter for measurement at 9 a.m. (±2 h) and 9 p.m. (±2 h) daily, or whenever the subject decides it is necessary. If the reading is less than 94%, the patient is considered to have severe illness and has reached the end point of the study and is recommended to seek medical attention immediately. Subjects are required to measure their oxygen saturation at rest until day 14 or the time of body temperature returning to normal (continuing for 24 h) or the negative conversion time (2 successive negative RAT results), whichever is later.

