
### Primary outcome

The time between starting medication and body temperature returning to normal (oral temperature 37.2°C and maintain 24 hours).

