### Sample size and statistical methods

#### Sample size estimation

The primary outcome of the study is the time between starting medication and body temperature returning to normal, i.e., the time to fever resolution after the first treatment. Based on previous studies, we assumed the standard deviation (SD) is 0.7, and the time to fever resolution of half a day (0.5 days) would have clinical significance (Qiu et al., 2020; Chen et al., 2021). Therefore, to detect such a difference between groups, 38 in each group will be needed with a power of 80% and a 5% 2-tail significance level. To allow for possible dropouts during the study period, we inflate this value by 20%, hence a total of 96 patients will be needed for the proposed study and 48 in each group (12 in each sub-group).

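### Time since fever onset is left out of the stratification and the stated model, although the primary outcome is remaining fever time and the 72-h entry clock does not measure it

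*Protocol article*

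**What the plan says.** All places are in the protocol article.

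- **Inclusion criteria, item 4:** "Duration of symptoms ≤72 h (Start from the presence of the major symptoms of COVID-19", with three alternative triggers: "Fever: oral temperature >37.2°C, or cough score ≥2, or fatigue score ≥2".
- **Inclusion criteria, item 5:** fever must be present at entry, "At the moment of screening (or within 2 h before screening), body temperature: >37.2°C". Nothing is said about how long it has been present.
- **Primary outcome:** "The time between starting medication and body temperature returning to normal". The Assessment section counts it in days: "Temperature recovery time is defined as the total number of days between medication starting date and the date of" the first sustained normal temperature, with both end days included.
- **Baseline randomization:** "the stratified randomisation is based on age" and number of vaccine doses, in four strata. The Abstract agrees: "after stratification according to age (A:18–49, B:50–65) and the number of vaccinations".
- **Statistical analysis:** groups are compared with a linear mixed model. The one covariate mentioned is western-medicine use, to be brought in only if the groups differ on it.
- **Sample size estimation:** "we assumed the standard deviation (SD) is 0.7, and the time to fever resolution of half a day (0.5 days) would have clinical significance", giving 38 evaluable and 48 recruited per group.
- **Table 1 and Baseline randomization:** screening is on day −1 to 0, and the medication is then sent by delivery service.

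**The concern.** In a self-limiting fever, the time still to run usually depends on the time already run. Take two subjects who both qualify at 70 h of symptoms. One has been febrile throughout; the other had cough first and became febrile an hour ago. Item 4 treats them alike, but their expected remaining fever differs unless fever duration is memoryless.

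The baseline variable closest to the outcome is therefore balanced only by chance, in a trial of 38–48 per arm, and it is not in the stated model. Two things are at stake: precision that could be recovered cheaply, and a chance difference between arms in time since onset that would pass straight into the unadjusted estimate. The symptom duration used for eligibility cannot stand in for the missing covariate, because it may have been started by cough or fatigue. The one covariate that is named is measured after randomisation and may itself respond to treatment, so it does not fill the gap.

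**Working it through.** **1. Range of fever time at entry.** Fever is itself a trigger, so fever cannot have lasted more than 72 h at screening. Item 5 only requires it to be present then. The range at screening is 0 to 72 h (0 to 3 days). Delivery of the medication can lengthen it by first dose.

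**2. The plan's own figure.** From the stated inputs (difference 0.5 days, SD 0.7 days, two-sided 5%, power 80%):

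n per group = 2 × [(1.960 + 0.842) × 0.7 / 0.5]² = 30.8, so 31 (32 with the t distribution).

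The article states 38. That errs on the safe side and is a separate matter. I use 38 per arm below because it is the planned evaluable number. The dropout step reproduces: 38 / 0.8 = 47.5, so 48.

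**3. Size of a chance imbalance.** *Assumption:* entry uniform over 0–3 days.

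- SD of entry time = 3/√12 = 0.87 days.
- SE of the arm difference in mean entry time = 0.866 × √(2/38) = 0.20 days.

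Entry requires that fever is still present, which lowers the SD to 0.82–0.86 days and the SE to 0.19–0.20 days.

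**4. How imbalance reaches the outcome.** *Assumptions, not in the article:* total fever duration T is gamma, entry time U is uniform on 0–3 days, and a subject is kept only if T > U. The outcome is T − U in continuous days, although the article counts whole days. The shift is |slope| × SE.

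| Mean, SD of T (days) | Slope of T − U on U | R² | Shift for a one-SE imbalance, 38 per arm | Share of 0.5 days |
|---|---|---|---|---|
| 3, 1.5 | −0.56 | 0.10 | 0.11 | 21% |
| 5, 2 | −0.87 | 0.13 | 0.17 | 34% |
| 4, 1.5 | −0.82 | 0.19 | 0.16 | 32% |
| 3, 1 | −0.76 | 0.30 | 0.14 | 29% |
| 4, 1 | −0.94 | 0.41 | 0.19 | 37% |

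With 48 per arm the shifts are 0.09–0.17 days. If T is exponential (memoryless), the correlation between U and T − U is zero and so is the shift.

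**5. Precision.** Adjusting for a baseline covariate with this R² multiplies the residual variance by 1 − R², that is by 0.90 down to 0.59. This is worth about 1/0.90 = 1.11 to 1/0.59 = 1.69 times the sample size.

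**6. Same check on the plan's own scale.** The outcome SDs in step 4 are 1.1–2.1 days, above the planned 0.7. If instead the outcome SD is 0.7 and R² is 0.10–0.41, the one-SE shift is √R² × 0.7 × √(2/38) = 0.05 to 0.10 days, or 10–20% of the target.

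**The case against.** The case against is substantial, and several parts of it stand.

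- **The entry rule is coherent.** A 72-h window with fever required at screening contains no error. A fever-only 72-h clock would leave the same 0–72 h range, so the composite trigger does not cause the spread. What it does is make the qualifying duration unusable as a measure of fever time. This stands.
- **Covariates and data fields are often left to other documents.** A plan that is not shown may adjust for onset, and the medical history taken at screening may contain it. The article does not say that fever onset goes unrecorded. This limits the point to an improvement on the model as stated; it is not proof of an omission. The article does, however, describe its adjustment strategy, and the one variable it chose is post-randomisation.
- **Randomisation protects validity.** It balances onset time on average, and an ordinary standard error already includes this variation. This stands: there is no systematic bias.

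A reader might infer two stronger claims that the documents do not support. The first is that a chance imbalance could be as large as the target effect. In every scenario above, a shift of 0.5 days or more has probability below 1%; the largest one-SE shift, 0.19 days, puts 0.5 days at 2.7 standard errors. The second is that the entry spread of 0.87 days exceeds the planned SD of 0.7 and so breaks the sample size. The 0.87 is the SD of an assumed entry time, while the 0.7 is an outcome SD taken from earlier studies and may already contain entry spread. A uniform spread also has to be wider than about 58 h (0.7 × √12 × 24) before it passes 0.7; over 48 h it is 0.58.

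**Conclusion.** The point holds as one of efficiency and chance imbalance. The eligibility clock does not measure fever time, the primary outcome is remaining fever time, and neither the stratification nor the stated model takes up time since fever onset. Under the assumed gamma durations and uniform entry, it explains about 10–41% of the outcome variance, and a one-SE imbalance moves the estimate by about 0.1–0.2 days, 20–40% of the 0.5-day target. If the planned SD of 0.7 is taken as correct, the shift is 0.05–0.10 days. If fever duration is memoryless, it is nil.

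These sizes rest on assumed distributions, since the article gives none. The conclusion that adjustment is worth making needs only that fever has a typical course. The finding does not invalidate the trial, the 72-h window or the sample size.

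**What to change.** Keep the 72-h criterion. At screening, record the date and time of fever onset as a field of its own, separate from the onset of cough and fatigue. Pre-specify hours from fever onset to first dose, and screening temperature, as baseline covariates in the primary between-group comparison, and include both whatever the observed balance. Measuring to first dose rather than to screening also captures the delivery delay.

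Applying items 4 and 5 already calls for an onset history and a temperature reading, so the cost is one extra field and two model terms, with no extra subjects or visits. Onset time is self-reported. Recall error will remain and will reduce the gain somewhat.
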